#### Secondary aims

Secondary aims seek to identify potential moderators and mediators of INTV, using data from assessment interviews and EMA. It is hypothesized that the influence of the intervention will be moderated by baseline readiness-to-change (for alcohol) and baseline GSAB questionnaire ratings of self-efficacy and planning (for both alcohol and pain outcomes). Secondary aims pertaining to alcohol use will be addressed by using baseline interview measures and parallel analyses will be conducted using baseline daily EMA ratings of readiness-to-change, alcohol coping self-efficacy, and alcohol-related planning. Mediational analyses will also be conducted using EMA at the 3-month outcome to test hypothesis that changes in self-regulatory processes mediate the effect of the INTV on alcohol use and chronic pain.

### Inclusion and exclusion criteria

Inclusion criteria will consist of the following: (1) at least 18 years of age; HIV + with confirmation via visual evidence of antiretroviral (ART) medication or medical record; (2) engaged in unhealthy drinking defined as: a) having more than 7 drinks for women or 14 drinks for men per week; or b) using an HIV specific index of heavy episodic drinking, having 3 or more drinks for women or 4 or more drinks for men on one occasion in the past month [31–33]; (3) experiencing moderate or greater chronic pain (a score of 4 or greater on the Numerical Pain Rating Scale [NPRS]) for at least three months per self-report); (4) own a smart phone; and live in the United States with a United States mailing address. Exclusion criteria are as follows: (1) a history of bipolar disorder, schizoaffective disorder, or schizophrenia per self-report; (2) an unstable dose of psychoactive medication for pain or alcohol/substance use [i.e., if on medication, participant has not been on same dose for least 2 months]; (3) a history of withdrawal-related seizures or delirium tremens per self-report; current non-pharmacological treatment for alcohol use disorder or chronic pain per self-report; (4) acute life-threatening illness that requires treatment or intention to have surgery for a pain-related condition in the next 6 months; (5) current cancer-related pain per self-report; (6) unwilling to provide sex at birth; (7) limited or non-reader; or (8) unable to provide one or more contacts to facilitate follow-up in case the participant cannot be reached.

### Recruitment, consent, and randomization

Recruitment will take place nationally via online advertisement in virtual patient communities, Google, Facebook, Instagram, health websites, and medical applications. BuildClinical (BC), a company that delivers study specific advertisements to various online platforms, regularly monitors metrics (i.e. percentage of potential participants who view and subsequently click an advertisement) to assess effectiveness and optimize the campaign to improve reach as necessary. When potential participants click on a study advertisement, a website populates containing general information about the trial and a link to a BC pre-screening form for those who are interested. BC pre-screening forms ask for contact information (name, e-mail, telephone number) and assess a preliminary subset of study eligibility criteria (e.g., HIV status, drinking habits, pain level).

If potential participants are eligible based on their responses to the preliminary BC pre-screening, research staff will contact the individual via phone call to confirm pre-screening questions and ask additional eligibility questions. At the time of consent, study staff will visually confirm HIV diagnosis via medical record or ART medication. Eligible and interested participants will take part in an informed consent process via videoconference or phone call and those who provide their consent electronically sign a REDCap [34, 35] form.

Randomization occurs after the baseline assessment phase is completed (described below) and is stratified by both gender and frequency of heavy drinking episodes. The project statistician will generate a list of randomization assignments to be used sequentially based on a permuted blocks strategy.

### Assessments

#### Assessment procedures

Assessments will include interview-administered instruments at baseline, 3 months post-randomization, and 6 months post-randomization. In addition, there will be two 15-day EMA data collection periods (one at baseline and one at 3-months), a treatment satisfaction measure, and a blood draw to test a biological marker of alcohol use, phosphatidylethanol (PEth; [29]) self-administered 6 months-post randomization.

Participants will complete all assessment interviews (baseline, 3-month follow-up, and 6-month follow-up) virtually through a videoconferencing platform or by phone. Interviews will take approximately 90 to 120 min and are each associated with $50 compensation for time and effort.

In addition to research interviews, participants will complete two phases of EMA data collection over 15-day periods. The first 15-day EMA period begins following the baseline interview while the second 15-day EMA period takes place following the 3-month assessment interview. Participants will learn about EMA procedures following the baseline interview, including how to use the EMA iOS or Android mobile application (MetricWire; [36]. Each day during the EMA periods, MetricWire will prompt participants to complete a morning survey and four additional surveys which arrive randomly throughout the day.

Upon completing the 15 days of EMA surveys at the 3-month time point, participants will be notified to complete one final survey on intervention satisfaction and acceptability for which they will be compensated $5. Across all study activities, participants will be able to earn up to $480 over the 6 months. Payments are made via electronic gift certificates.

Finally, at the 6-month outcome assessment interview, participants will be able to earn an additional $25 for completing and sending a self-administered blood sample to the collaborating laboratory [29].

#### Assessment instruments

##### Sociodemographic characteristics

Sociodemographic information will be collected during screening and baseline interview and includes the following: age, state and zip code, sex assigned at birth, gender identity, height, weight, sexual orientation and whom they have sex with in their life (men only, women only, both men and women, not had sex), marital status, current spouse/partner, ethnicity, race, primary language, education, employment, insurance, difficulty paying bills, and unhoused status.

##### Alcohol assessment measures

The primary outcomes for alcohol use include number of alcoholic drinks consumed per week and number of heavy episodic drinking days in the past month (assessed via Alcohol Timeline Followback – 30 days [TLFB-30]; [37, 38]). Alcohol-related consequences will also be assessed using the Short Inventory of Problems-Revised (SIP-R; [39]) as a secondary outcome. A series of measures related to the self-regulation of alcohol use will also be administered, including the Readiness to Change Questionnaire (RTCQ; [40] and Goal Systems Assessment Battery (GSAB; [41, 42]), which provides assessment of value, self-efficacy, self-monitoring, and planning related the goal of moderating alcohol use.

##### Pain assessment measures

The primary outcome for pain is a composite measure of pain severity and interference (pain average, interference with enjoyment of life, and interference with general activity [PEG]; [30]). More comprehensive indices of pain intensity and pain interference will also be assessed using the Brief Pain Inventory- Short Form (BPI; [43]). The GSAB for pain will also be administered to assess self-regulatory components related to the goal of pain management, specifically planning and self-efficacy [41, 42].

##### EMA

As noted above, participants will complete two 15-day periods of EMA: one following the baseline interview and one following the 3-month interview assessment. Each day, participants will complete a morning survey and a set of 4 shorter random surveys. Compensation for completing EMA surveys is $3 for each morning survey and $1 for each random survey. Those who complete all 5 EMA surveys on any given day receive a $3 bonus. Participants can earn up to $10 per day for completing EMA surveys, with a maximum total of $150 per 15-day EMA span ($300 for both timepoints). EMA surveys were modified from previous EMA studies (e.g., [27, 44, 45]) to include questions about alcohol use [46, 47], chronic pain [30], physical and mental functioning [48–50], affect [51, 52], sleep [53], other substance use (i.e., cannabis and tobacco; [54, 55]), and self-regulatory processes [41, 42] that underlie pain management and drinking. EMA data will be collected via MetricWire, a smartphone application that is downloaded onto participants’ phones. Participants will be given the option to use their own email and private password or use a study provided email and password to access the program. The EMA surveys will consist of two assessment types, a morning survey and random survey. Morning surveys will be available from 4am to 10:30am and are initiated by the participant to report aggregate experiences over the past 24 h. Two reminders will be sent within that block to confirm the availability of the morning survey which will take approximately 5 min to complete. Random surveys are signal-contingent recordings whereby participants respond to prompts about their current pain, physical activity, alcohol and other substance use, and affect. They occur randomly in 3-hour blocks (e.g., 9am-noon; noon-3pm; 3-6pm; 6-9pm) and will take approximately 3 min to complete.

##### Phosphatidylethanol

PEth biomarker tests will be used as a marker of unhealthy alcohol use, and is an additional outcome to supplement self-report outcome measures [56]. Blood samples will be collected by the participants using a Tasso-M-20 device [57] with guidance from research assistants. The device uses a button that sticks to the skin, typically on the shoulder. When the instrument is pressed, a lancet pierces the skin and draws blood from the capillaries into a container at the bottom of the device. This procedure produces little discomfort and can be used with minimal training.

The full set of assessments is presented in Table 1.

**Table 1 Tab1:** Enrollment, intervention, and assessment schedule

TIMEPOINT	Enrolment	Baseline	Randomization	Month 3	Month 6
**Enrolment**					
Eligibility Screen	X				
Informed Consent	X				
Allocation			X		
**Intervention**					
Motivational and Cognitive-Behavioral Management for Alcohol and Pain (INTV) *or*				X	X
Information-Only Control (CTL)				X	X
**Assessments**					
Sociodemographic Characteristics		X			
Current Medications, Medication History		X		X	X
HIV Viral Load		X			X
Treatment Induced Neuropathy Assessment Scale [58]		X		X	X
Alcohol Timeline Followback – 30 days^†^ [37, 38]		X		X	X
Short Inventory of Problems – Revised, Alcohol^†^ [39]		X		X	X
Alcohol Use Disorder Identification Test (Consumption Questions)^†^ [59, 60]		X		X	X
Social Network Drinking^†^ [61]		X		X	X
Addiction Severity Index – 30-day illicit drug use^†^ [62]		X		X	X
CDC Smoking and Vaping Assessment [63]		X		X	X
Alcohol, Smoking and Substance Involvement Screening Test^††^ [64]		X		X	X
Pain, Enjoyment of life, and General Activity assessment^§^ [30]		X		X	X
Brief Pain Inventory – Short Form^§^ [43]		X		X	X
Physical Activity Questionnaire^§^ [65]		X		X	X
International Physical Activity Questionnaire^§^ [66]		X		X	X
Goal Systems Assessment Battery – Pain^§,††^ [41, 42]		X		X	X
HIV Symptom Index [67]		X		X	X
HIV Risk Behaviors [68]		X		X	X
Berger HIV Stigma Scale [69]		X		X	X
Discrimination and Stress Scales [70–72]		X		X	X
Modified Positive and Negative Affect Schedule^¶^ [51]		X		X	X
Revised UCLA Loneliness Scale^¶^ [73]		X		X	X
Perceived Stress Scale^¶^ [74]		X		X	X
Patient Health Questionnaire – 8^¶^ [75]		X		X	X
Generalized Anxiety Disorder – 7^¶^ [76]		X		X	X
Veterans RAND 12 Item Health Survey^¶^ [77]		X		X	X
Patient-Reported Outcomes Measurement Information System (PROMIS) Sleep Disturbance^¶^ [78]		X		X	X
AIDS Clinical Trials Group Falls Questionnaire^¶^ [79]		X		X	X
Goal Systems Assessment Battery – Alcohol^†,††^ [41, 42]		X		X	X
Readiness to Change Questionnaire – Alcohol^††^ [40]		X		X	X
Phosphatidylethanol (PEth) [56]					X
Ecological Momentary Assessment (15 days)		X		X	
Treatment Satisfaction [80]				X	
Treatment Utilization					X

^†^, alcohol and other substance use outcomes

^§^, pain outcomes

^¶^, physical and mental health

^††^, potential mediators and moderators of behavior change for pain and alcohol use

### Study conditions

#### Intervention

##### Rationale for integrated videoconferencing intervention

There would be considerable benefit to have an integrated approach to treat unhealthy alcohol use and pain for utilization across a variety of health care and community settings. Self-management interventions grounded in CBT have proven efficacious in reducing alcohol use and chronic pain across a wide range of populations [81, 82]. In the context of chronic medical conditions, these approaches emphasize strategies for addressing motivation to change and developing cognitive-behavioral skills for initiating and maintaining change [83]. Integrated interventions provide the opportunity to condense the number of sessions through common underlying treatment targets (e.g., stress coping) as well as helping patients understand the associations between pain and alcohol use in their own lives.

Telehealth through a videoconferencing platform represents an increasingly available method of intervention delivery that can enhance treatment access and adherence [84]. Telehealth has proven particularly advantageous among populations facing significant barriers to treatment, such as non-urban and low-income individuals, and has gained similar levels of treatment satisfaction compared to in-person treatment [85–89]. Second, the web-based formatting facilitates patient connection to supplemental materials (e.g., web-based assessments, EMA, video-skills training) that may extend interventions [84, 85]. Overall, this approach provides greater flexibility in terms of how and when interventions may be delivered.

##### INTV structure and content

The INTV utilizes a self-regulation framework [90] to integrate evidence-based approaches for chronic pain and unhealthy drinking. Specifically, INTV integrates Motivational Interviewing (MI; [91]) and cognitive-behavioral skill training [92, 93] for unhealthy drinking with cognitive-behavioral and self-management approaches for chronic pain [82, 94]. These approaches have proven efficacious for reducing unhealthy drinking and chronic pain as individual treatment targets among PLWH [95, 96]. The central goals of INTV are to increase motivation and self-efficacy to change and provide cognitive and behavioral skills to manage pain and reduce alcohol use. The intervention will be delivered through internet-based videoconferencing and supplemented with web-based content. The initial treatment session provides a rationale for addressing alcohol and pain together in the context of HIV management, and initiates MI related to alcohol use. Over the subsequent weeks, participants receive 6 additional treatment sessions, each lasting 45–60 min, for a total of 7 sessions (see Table 2). The intervention content was adapted for PLWH through a mixed methods approach and underwent preliminary testing to assess feasibility and acceptability [95, 96].

**Table 2 Tab2:** Overview of intervention content

Session #	Brief Content Description
Session 1	Introduction to Intervention: Provide psychoeducation about alcohol and pain, deliver brief motivational intervention for alcohol, explain rationale for intervention approach, set initial goals, and review technology requirements.
Session 2	Behavioral Activation: increasing pleasant events, considering personal life goals and the role of alcohol.
Session 3	Identifying triggers of pain and factors that reduce pain; review diaphragmatic breathing, progressive muscle relaxation, imagery, and self-monitoring.
Session 4	Identifying unhelpful (automatic) thoughts and beliefs; review cognitive restructuring, managing negative thoughts related to stress, and the relationship between negative affect and pain
Session 5	Review planning, time-based pacing, and alcohol-related coping skills, with emphasis on harm reduction skills
Session 6	Discuss sleep hygiene and the influence of lifestyle factors on pain and stress
Session 7	Review of skills; discuss continuing self-management beyond treatment and successes, challenges, and barriers.

*Note*: https://sites.bu.edu/mhealth/ contains supplementary material accompanying each session

#### Control

Participants randomized to CTL will meet once with an interventionist (“health counselor”) via videoconferencing for 20–30 min and receive psychoeducation about the effects of alcohol and pain on HIV symptoms, recommendations for alcohol use reduction, and a list of treatment resources for alcohol and chronic pain. CTL participants complete the same research assessments as those in INTV.

##### Rationale for control condition

The choice of this control condition was based on our goal to obtain an estimate for the impact of INTV compared to the current standard of care. We believe that psychoeducation and brief advice serves as an optimal control condition at this stage of intervention efficacy testing because it provides a test of whether the proposed intervention provides benefit compared to the type of intervention that may be commonly provided as part of an HIV-care visit (treatment-as-usual) or community setting. We recognize that different control conditions offer different types of information relevant to the efficacy and effectiveness of an intervention and that alternative control conditions (e.g., weekly contact) may be utilized in the next stages of research should this approach prove to demonstrate evidence of efficacy.

### Interventionist training, Supervision, and Fidelity Assessment

Interventionists will be clinical psychologists and advanced level PhD clinical psychology students trained in both INTV and CTL condition content. Training will include MI in medical settings, [91] CBT for pain, [94] and alcohol self-management [92, 93]. Interventionists will participate in trainings on the INTV manual, supplemented by video recordings, role plays, and structured training cases. Supervision will occur on a biweekly basis, during which individual cases will be discussed. Interventionists also will conduct post-intervention fidelity assessments. Sessions will be digitally recorded with participant consent and select cases may be reviewed by interventionists and supervisors as needed.

### Statistical design and analysis

#### Sample size determination

A sample size of 250 (*n* = 125 to each condition) will be randomized. With a conservative estimate of a 20% attrition rate by 6-month follow-up, this sample size gives power (80%) to detect medium effects (Cohen’s d = 0.40) at the 2-tailed significance level (0.05) for INTV versus CTL at 6-month follow-up on both pain and alcohol outcomes. The anticipated effect size is based on the following: (1) meta-analyses of CBT interventions compared to assessment and minimal interventions suggesting medium post-intervention effects on alcohol and pain; [98–100] and (2) results of our pilot study which showed medium-to-large pre-to-post changes (Cohen’s d from 0.79 to 1.0) within participants receiving INTV [95, 96]. Moreover, the availability of repeated measurements (to include a baseline covariate) increases statistical power to detect intervention effects for the analysis.

#### Primary and secondary analyses

Descriptive statistics will be provided for the baseline characteristics of the full sample and by condition (i.e., INTV vs. CTL). Multiple linear regression analyses will be used to test whether those in the INTV group consume fewer drinks per week, engage in fewer episodes of heavy episodic drinking, and report lower PEG ratings than those in the CTL group at 6-month outcome. Covariates will include age, sex at birth, and corresponding baseline measures of alcohol use and pain. Secondary analyses will examine related outcomes (i.e. alcohol related consequences, pain intensity, pain severity) using a parallel approach. Exploratory analyses will examine INTV effects on outcomes including substance use frequency, depressive symptoms, anxiety symptoms, HIV symptom index scores, HIV risk-taking behaviors, mental functioning, and physical functioning at 6 months using multivariate regression models. For PEth analyses, we will use the lower limit of quantification as a cut-off of > 50 as a measure of unhealthy alcohol use and a cutoff of PEth > 8 ng/ml) as a marker of any alcohol use. Logistic multiple regression with the age and race/ethnicity will be used to examine intervention effects on 6-month PEth outcomes [101]. Secondary aims will be addressed, in part, by using baseline interview measures of readiness-to-change (for alcohol) and baseline GSAB questionnaire ratings of self-efficacy and planning (for both alcohol and pain outcomes). Planned covariates include those described under primary aims and will include baseline values of the questionnaire measure being evaluated. The Condition x Moderator term will be added to the full models to examine interaction effects, which will be followed with simple slopes analyses to determine the direction of effects.

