### Overall design

Participants will be PLWH who engage in unhealthy drinking and experience moderate or greater chronic pain recruited nationally via online advertisement. Those who are eligible based on an initial set of online prescreening questions will be contacted by study staff for a more comprehensive phone screening. Those who remain eligible based on the more extensive screening will be scheduled for baseline assessment during which they will provide informed consent, confirm HIV diagnosis, and complete baseline questionnaires administered in an interview format. Staff will also orient participants to the EMA procedures whereby they will complete 5 surveys per day for the following 15 days. After EMA data collection, participants will undergo 1:1 randomization into either the intervention group (INTV) or the control (CTL) group. The INTV condition is a 7-session program designed for weekly delivery through videoconferencing by a health coach. Those in the CTL group meet virtually with the health coach for a single session and be provided with information and resources about alcohol and pain. At three-month outcome assessment, staff will administer questionnaires via interview, prior to another 15 days of EMA data collection. The final study assessment occurs six months after randomization and will include a staff-administered interview and a self-collected blood draw to measure phosphatidylethanol (PEth), a biological marker of alcohol use (see [29]). Participants complete self-collected blood draws at home and with guidance through videoconferencing (Fig. 1).

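### The primary models do not name the 15 days of pre-randomisation EMA pain and drinking ratings as covariates: a missed efficiency, mainly for PEG, not an error or a bias

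*Protocol article*

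**What the plan says.** **Primary models.** Under Primary and secondary analyses, the three primary outcomes (drinks per week, heavy drinking episodes and PEG at 6 months) are compared by multiple linear regression. The covariates are stated: "Covariates will include age, sex at birth, and corresponding baseline measures of alcohol use and pain". The Primary aim section ties the adjustment to the baseline value of each outcome. The Alcohol assessment measures section takes both drinking outcomes from the 30-day Timeline Followback (TLFB-30). The Pain assessment measures section defines PEG as a three-part composite.

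**Timing of EMA.** The first 15-day EMA period follows the baseline interview and ends before allocation: "After EMA data collection, participants will undergo 1:1 randomization". There are five surveys a day.

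**Content of EMA.** The EMA section says that the surveys were adapted "to include questions about alcohol use [46, 47], chronic pain [30], physical and mental functioning", among other topics. The source cited for the EMA pain items is the one cited for PEG.

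**Planned use of EMA.** The Secondary aims and EMA data analysis sections give baseline EMA to moderation by readiness, self-efficacy and planning. The 3-month EMA goes to mediation, and there are exploratory event-level analyses. No section puts the baseline EMA pain or drinking ratings into a primary model.

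**The concern.** The trial collects up to 5 x 15 = 75 surveys per person before randomisation, at up to $150 each, and they measure the same constructs as the primary outcomes. A mean over many days averages out day-to-day fluctuation that a single-occasion interview score carries. It may therefore explain part of the 6-month variance that the interview score does not. The Sample size determination section itself argues that a baseline covariate adds power, and the same reasoning extends to a second, more heavily averaged baseline measure.

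What is at stake is the width of the confidence intervals on the primary contrasts, chiefly for PEG. Validity is not at stake. A covariate measured before randomisation does not bias the randomised comparison, whether it is included or left out.

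**Working it through.** **1. The plan's own figure.** Inputs from Sample size determination: 250 randomised (125 per arm), 20% attrition, d = 0.40, two-sided 0.05.

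- Completers per arm: 125 x 0.80 = 100.
- Power from the noncentral t distribution, 198 df, noncentrality 0.40 x sqrt(100/2) = 2.83: **80.4%** (80.7% by the normal approximation).

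The stated 80% reproduces with no covariate at all.

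**2. Formulas.** Let B be the interview baseline, E the EMA person-mean and Y the 6-month outcome. The documents give none of the correlations, so every r below is assumed.

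- B alone: R2 = rBY^2.
- B and E: R2 = (rBY^2 + rEY^2 - 2 rBY rEY rBE) / (1 - rBE^2).
- Cut in residual variance = 1 - (1 - R2 with E) / (1 - R2 without E).
- Power: step 1 with d replaced by 0.40 / sqrt(1 - R2).

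**3. Interview baseline alone.** With rBY = 0.5, R2 = 0.25 and power is **90.1%**. This is the starting point for the tables below.

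**4. Adding the EMA mean, correlations set directly** (rBY = 0.5). Example, rEY = 0.5 and rBE = 0.7: R2 = (0.25 + 0.25 - 0.35) / 0.51 = 0.294; cut = 1 - 0.706/0.75 = 5.9%; power 91.8%; equivalent completers 200 x 0.75/0.706 = about 213.

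| rEY | rBE = 0.5 | 0.6 | 0.7 | 0.8 |
|---|---|---|---|---|
| 0.4 | 4.0% (91.3%) | 2.1% (90.7%) | 0.7% (90.3%) | 0.0% (90.1%) |
| 0.5 | 11.1% (93.2%) | 8.3% (92.4%) | 5.9% (91.8%) | 3.7% (91.2%) |
| 0.6 | 21.8% (95.7%) | 18.8% (95.0%) | 16.3% (94.4%) | 14.8% (94.1%) |

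Cells show the variance cut, with power at d = 0.40 in brackets.

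**5. Adding the EMA mean, built up from days.** Here rBY is again 0.5. Let c be the day-to-day correlation and q the correlation of one EMA day with Y, and let the interview score correlate c with each EMA day. The variance of a 15-day mean is v = (1 + 14c)/15, so rEY = q/sqrt(v) and rBE = c/sqrt(v). All 15 days are assumed complete.

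| q | c = 0.5 | 0.6 | 0.7 | 0.8 |
|---|---|---|---|---|
| 0.50 | 29.4% (97.2%) | 20.0% (95.3%) | 13.0% (93.6%) | 7.7% (92.3%) |
| 0.45 | 18.8% (95.0%) | 11.3% (93.2%) | 5.8% (91.8%) | 1.9% (90.7%) |
| 0.40 | 10.6% (93.0%) | 5.0% (91.5%) | 1.4% (90.6%) | 0.0% (90.1%) |

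The top row treats the interview PEG as worth no more than one EMA day. Lowering q by only 0.05 removes a third or more of the gain in every column.

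**The case against.** **Adjusting each outcome for its own baseline is standard, unbiased and enough for the planned power.** This stands. A reader might infer that the primary analysis is biased or underpowered. The documents do not support that, since 80% is reached with no covariate.

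**The models do not adjust only for an interview value.** This also stands. Age and sex at birth are included, and the text speaks of baseline measures without naming the interview. Randomisation follows a baseline phase that contains EMA, and Table 1 marks EMA in the Baseline column. The interview reading is still the natural one: the adjustment is tied to the outcomes' own baseline values, and the Secondary aims section distinguishes interview measures from EMA ratings when EMA is meant. It remains an inference.

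**The size is uncertain.** A reader might infer a definite loss near the 29% end. That figure needs days within one fortnight to correlate no more strongly than one day does with the outcome six months later. It also needs complete EMA, and an interview PEG exchangeable with one EMA day. PEG is a composite, and its baseline uses the same instrument and interview format as the 6-month outcome, so it may predict better than one day does. Near-zero gain is possible.

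**The gain is not equal across outcomes.** TLFB-30 already aggregates 30 days, twice the EMA window, so the case for the two drinking outcomes is weaker.

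**A condensed article may leave covariate construction to an analysis plan.** This holds for derivation rules. The article does, however, state a covariate list, and the point is a suggested addition to it.

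**Conclusion.** The point holds as a low-cost improvement of minor importance. Pre-randomisation EMA measures of pain and drinking are collected, and the primary models do not name them as covariates. With an assumed interview-baseline correlation of 0.5, 100 completers per arm and d = 0.40, the residual variance cut is:

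- about 0% if EMA predicts less well and largely repeats the interview value;
- roughly 4% to 16% under moderate correlations;
- about 20% to 29% only under favourable assumptions.

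Power moves from about 90% to between 90% and 95% in most of these cases. Missed surveys would lower the gain. Confidence in any single figure is low because no correlation is documented. Confidence that the addition does no material harm is high.

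**What to change.** Before any unblinded analysis, add a sentence to the analysis plan:

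- In the PEG model, keep the interview baseline and add the person-mean of the pre-randomisation EMA pain ratings.
- Optionally, do the same in the two drinking models, with mean daily drinks and the proportion of EMA days with heavy drinking.
- Average whatever days were completed. For participants with no EMA, fill the covariate with the overall mean and add a missing indicator, so that nobody is dropped.
- Use no 3-month EMA as a covariate, because it is measured after randomisation.

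The cost is one derived covariate per model, one or two degrees of freedom out of nearly 200, and a rule for sparse EMA. No new data are needed, and fixing the choice in advance avoids selecting covariates after the results are known.

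### The PEth plan attaches the assay's quantification limit to the > 50 cut-off and names only yes/no analyses, which costs power in the one biological check on reported drinking

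*Protocol article*

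**What the plan says.** All references are to the protocol article.

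- **Cut-offs (Primary and secondary analyses).** The higher one is introduced with "we will use the lower limit of quantification as a cut-off of" > 50, for unhealthy use. The lower one reads "a cutoff of PEth > 8 ng/ml) as a marker of any alcohol use". Only the second carries a unit.
- **Model (same section).** A logistic model with age and race/ethnicity as covariates "will be used to examine intervention effects on 6-month PEth outcomes". No quantitative, ordinal or censored PEth analysis is named.
- **Role (Phosphatidylethanol).** PEth "is an additional outcome to supplement self-report outcome measures". It is not among the primary outcomes listed under Primary aim.
- **Timing (Assessment procedures and Table 1).** The sample is "self-administered 6 months-post randomization". Table 1 shows no baseline PEth.

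No other section gives the assay's lower limit of quantification.

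**The concern.** There are two separate issues.

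**Wording.** The sentence makes the quantification limit the > 50 threshold and then uses a threshold below it. If the limit is 50, results between 8 and 50 have no reliable value and the > 8 rule cannot be applied. If the assay quantifies down to 8, then 50 is not its limit. Either way one phrase is wrong.

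**Analysis.** The primary drinking outcomes are self-reported in a behavioural trial whose participants know what they receive. PEth is the one measure that does not depend on report. The plan analyses the self-reported outcomes quantitatively by linear regression but reduces the biomarker to yes or no. If INTV lowers PEth without moving many people across 8 or 50, PEth may fail to corroborate a real effect, and a null PEth result would be hard to interpret.

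**Working it through.** **Step 1. The plan's own figure.** Sample size determination gives 250 randomized, 20% attrition, d = 0.40 and two-sided 0.05. That leaves 125 × 0.80 = 100 per arm. Power = Φ(0.40 × √(100/2) − 1.960) = Φ(2.828 − 1.960) = Φ(0.868) = 80.7%, so the stated 80% reproduces. It applies to a continuous comparison. No power is stated for PEth.

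**Step 2. What a cut costs in general.** Assume log-PEth is normal, so a cut with control proportion p above it sits at z = c. Its efficiency relative to the continuous comparison is φ(c)²/[p(1 − p)]. For a median split this is 0.3989²/0.25 = 0.64. At p = 80%, 90% and 95% it is 0.49, 0.34 and 0.22. One cut therefore loses at least about 36% of the information.

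**Step 3. The two planned cuts.** The article gives no PEth distribution, so these inputs are assumptions: log-SD 1.4, control median m of 20, 60 or 120 ng/mL, both cut-offs in ng/mL, and an INTV shift of 0.40 SD (0.40 × 1.4 = 0.56 log units).

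- Control proportion above cut-off k: p₁ = 1 − Φ(z), with z = (ln k − ln m)/1.4.
- INTV proportion: p₂ = 1 − Φ(z + 0.40).
- Power = Φ[(p₁ − p₂ − 1.960 × se₀)/se₁], with se₀ pooled and se₁ unpooled.

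Example with m = 60, k = 50: z = (3.912 − 4.094)/1.4 = −0.130, so p₁ = 0.552 and p₂ = 0.394. Then se₀ = √(0.473 × 0.527 × 2/100) = 0.0706 and se₁ = 0.0697. Power = Φ[(0.158 − 0.138)/0.0697], which is 61% before rounding of the inputs.

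| Control median (ng/mL) | > 50: CTL vs INTV | Power | > 8: CTL vs INTV | Power |
|---|---|---|---|---|
| 20 | 25.6% vs 14.6% | 50% | 74.4% vs 60.0% | 58% |
| 60 | 55.2% vs 39.4% | 61% | 92.5% vs 85.1% | 38% |
| 120 | 73.4% vs 58.9% | 58% | 97.4% vs 93.8% | 23% |

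**Step 4. Simulation under the same assumptions, without baseline adjustment.** Power is about 50-63% for > 50, about 10-60% for > 8, and about 77-83% for Tobit regression of log-PEth left-censored at 8. The Tobit range straddles the 80.7% of Step 1 within simulation error. The one clear gap from the formula is > 8 at a median of 120. Only about 3 and 6 people per 100 are then expected at or below 8, the normal approximation is poor, and the logistic Wald test reaches about 10% rather than 23%.

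**Step 5. Missing samples.** If a further 20% of samples are lost (80 per arm), the continuous comparison has 71.6% power. A yes/no comparison has 26-52% for control proportions of 50% to 95% above the cut.

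**The case against.** **The wording slip is near-clerical.** This largely stands. Two cut-offs for two constructs are legitimate, the unmatched bracket suggests an editing error, and an analyst would still cut at 50 and 8. A reader might infer that the thresholds contradict each other. They do not; only the quantification-limit label conflicts with the lower one.

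**Cut-offs suit a marker, and a condensed article may leave a quantitative analysis to the full plan.** This stands in part. The cut-offs are interpretable and worth keeping. But the article names its PEth method, so the comment addresses a stated choice. If the full plan already contains a quantitative analysis, one added sentence settles it.

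**The loss rests on an unknown distribution.** Its size does; its direction does not, since every control proportion and median tried showed a loss. Analysing both cut-offs also keeps somewhat more information than either alone.

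Three stronger readings are tempting and are not supported:

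- *That > 8 must sit at its ceiling because everyone enrolled drinks unhealthily.* The inclusion criteria admit people on a single past-month occasion of 3 or more drinks (women) or 4 or more (men), so low values are plausible. At a median of 20, > 8 is the more powerful of the two cuts.
- *That a quantitative analysis would reach about 90% power.* That requires adjustment for baseline drinking, which the PEth model does not list.
- *That the cut-offs hide individual falls in PEth.* With a month-6 sample only, no analysis can show within-person change. The loss is in the comparison between arms.

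**Conclusion.** The point holds on two counts of different weight. The quantification-limit phrase is attached to the wrong threshold or carries the wrong value, and the unit for 50 is missing. That is certain from the text and minor. Naming only logistic models for PEth is an inefficient choice. For a 0.40 SD effect it lowers power from roughly 77-83% to 50-63% (> 50) or 10-60% (> 8), and which cut-off is weaker depends on the unknown PEth distribution.

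These figures assume log-normal PEth, log-SD 1.4, control medians of 20-120 ng/mL, 100 evaluable samples per arm, censoring at 8, and that the effect size planned for the pain and alcohol outcomes carries over to log-PEth. None of the PEth inputs comes from the article.

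PEth is supportive and the trial is not sized on it, so the primary conclusions are unaffected. Severity is low to moderate.

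**What to change.** 1. State the assay's lower limit of quantification once, with its unit, as confirmed by the laboratory.
2. State the two cut-offs separately from it: > 50 ng/mL for unhealthy use and > 8 ng/mL for any use, confirming the unit for 50.
3. Make the main PEth comparison a Tobit regression of month-6 log-PEth, left-censored at the quantification limit, with the covariates already named. Keep both logistic analyses as supporting results.
4. Fix this before outcome data are examined, so that the PEth definition is not chosen after the fact.

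Cost: a few sentences of analysis text, with no extra samples or visits. The effect is also reported as a ratio of concentrations, which is less familiar than percentages. The model assumes roughly log-normal PEth, which should be checked. The laboratory must report concentrations; the ng/ml cut-off implies this, but the article does not say so.
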